### Outcomes

Primary, secondary and exploratory outcomes are outlined in table 2, box 1.

**Table 2 T2:** Procedures in the trial that are in addition to standard care (alongside ‘treatment as usual’)

Procedure	Time/visit	Dosage/volume
BCT/Befriending sessions	Baseline and 4 weeks later	60 min initial session; 30 min second session
Seizure frequency diary	Completed by the participant as seizures occur throughout the 24-week study period	~1 min per week
Breathing exercises (BCT participants only) and adherence diary	Following the baseline session, through to Week 12	5–10 mins, two times a day
Self-report questionnaires	Baseline, Week 4, Week 12 and Week 24	30–45 mins
LEDS (optional)	Week 12	LEDS (optional) Week 12 ~2 hours

BCT, breathing control training; LEDS, Life Events and Difficulties Schedule.

Box 1OutcomesPrimarySeizure remission, defined as seizure frequency of zero in the preceding 4 weeks (recorded by the participant in a seizure frequency diary), measured at Week 12 (12 weeks post the initial treatment session).SecondaryChanges in hyperventilation from baseline, measured by the Nijmegen scale of hyperventilation provided at baseline, Week 4, Week 12 and Week 24.Changes in healthcare utilisation from baseline, measured via a tailored resource use questionnaire provided at baseline, Week 12 and Week 24, as well as changes in health service use ascertained from Services Australia and CVDL data (Services Australia and CVDL data for consenting participants only).Changes in quality of life from baseline, measured by the Assessment of Quality of Life Eight Dimension provided at baseline, Week 4, Week 12 and Week 24.Changes in depression and anxiety symptoms from baseline, measured by the 9-item Patient Health Questionnaire and Generalised Anxiety Disorder Assessment respectively, provided at baseline, Week 4, Week 12 and Week 24.Changes in occupational and social functioning from baseline, measured by the Work and Social Adjustment Scale provided at baseline, Week 4, Week 12 and Week 24.Acceptability of BCT captured by a tailored self-report questionnaire provided after attending the Week 4 ‘booster’ session.Safety of BCT assessed by the occurrence of adverse events reviewed at Week 4, Week 12 and Week 24.tcCO_2_ levels (mm Hg; a marker of hyperventilation) preceding or during seizures, BPAT score (at baseline) and/or Nijmegen score (at baseline), to predict response to treatment.ExploratoryThe presence of significant life events in childhood and adolescence (≤16 years of age), and 12 months preceding the onset of their FS, assessed via the Childhood Experience of Care and Abuse Questionnaire and the LEDS*, respectively, to gauge moderators of treatment response.The MDI and Toronto Alexithymia Scale provided at baseline will be assessed if predictors of treatment response. MDI scores at Week 4, Week 12 and Week 24 will be assessed if they correlate with treatment response.*Note, the LEDS is optional, and only relevant to participants whose FS have started within the last 2 years.BCT, breathing control training; BPAT, Brompton Breathing Pattern Assessment Tool; CVDL, Centre for Victorian Data Linkage; FS, functional seizures; LEDS, Life Events and Difficulties Schedule; MDI, Multiscale Dissociation Inventory; tcCO_2_, transcutaneous carbon dioxide.

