#### Measures

In addition, the following measures and standardised clinical questionnaires will be used in the trial (see table 3, box 2, for scheduling). All self-reported questionnaires will be completed via REDCap.

**Table 3 T3:** Participant timeline

Assessment/ procedure	Clinical assessment (neurologist)*	Prescreening	Initial session with physio (baseline)	‘Booster’ session (Week 4) with physio	Follow-up (Week 12†)	Follow-up (Week 24)	Week 52, 78 and 104 observational follow-up (optional)
Video EEG	x						
tcCO_2_ monitoring	x						
FS semiology and chronicity	x						
Medical hx (inc. family hx and psychiatric hx)	x						
Informed consent		x					
Confirm eligibility		x					
BCT/Befriending intervention			60 mins X	30 mins X			
Seizure frequency diary		For preceding 4 weeks	Recorded by the participant throughout the 24-week trial period (automated reminders sent weekly via text/email, or daily via MyCap)				For preceding 4 weeks
Seizure control and triggers		x			x		
Seizure quality		x		x	x		
Demographics		x					
AQoL-8D		x		x	x	x	x
Nijmegen scale		x		x	x	x	x
GAD-7		x		x	x	x	x
PHQ-9		x		x	x	x	x
WSAS		x		x	x	x	x
TAS		x					
MDI		x		x	x	x	x
RUQ		x			x	x	x
Adverse events				x	x	x	
Acceptability questionnaire				x			
LEDS (optional)					x		
CECA-Q					x		

* Standard care

† Primary endpoint

AQoL-8D, The Assessment of Quality of Life 8 Dimension; BCT, Breathing Control Training; CECA-Q, Childhood Experience of Care and Abuse Questionnaire; EEG, electroencephalogram; FS, functional seizures; GAD-7, Generalised Anxiety Disorder Assessment; Hx, history; LEDS, Life Events and Difficulties Schedule; MDI, Multiscale Dissociation Inventory; PHQ-9, Patient Health Questionnaire, 9-item; RUQ, Resource Use Questionnaire; TAS, Toronto Alexithymia Scale; WSAS, Work and Social Adjustment Scale.

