##### Patient Health Questionnaire, 9-item

A 9-item self-report questionnaire used to aid in the diagnosis of depression, as well as monitoring the severity of symptoms. Items correspond to the DSM-IV diagnostic criteria for major depressive disorder. Responders are asked to rate how much they have been bothered by each item based on the previous 2 weeks via a 3-point Likert scale (0=not at all; 3=nearly every day). An overall severity score is obtained by totaling the 9 items (mild depression: 5–9; moderate depression: 10–14; moderately severe depression: 15–19; severe depression: 20–27). The Patient Health Questionnaire, 9-item is estimated to take 1–2 min to complete.^34^

A tailored RUQ developed by health economists from Monash University (Melbourne, Australia) will ascertain participants’ utilisation of healthcare resources and lost productivity in the previous 3 months. This includes items which explore medication use, emergency department presentations, ambulance assistance, hospitalisations and clinician visits. The RUQ is expected to take 5–8 mins to complete.

Participants randomised into the BCT group will be provided with a second diary to record if and when they complete their BCT home exercises up until primary endpoint (Week 12). This diary will also be available to complete on MyCap. If the latter, participants will receive a daily notification on their smartphone/tablet device asking them ‘did you complete your BCT homework yesterday?’ (yes/no).

Participants completing pen and paper diaries (or electronically on a computer) will be reminded by the physiotherapist to return the first month’s diary at the ‘booster’ session for review. Thereafter, at the end of each monthly cycle until Week 24, participants will be contacted by study staff (emailed/texted) and asked to return their seizure diary (via email/post as they prefer). If participants do not respond to the email/text, they will be telephoned by study staff within 5 days to assist gathering this data. A copy of the diary will be uploaded into REDCap and FS frequency for the preceding 4 weeks calculated.

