#### Primary outcome

FS remission (table 2) will be analysed using a random intercept logistic regression model, including in the model factors visit, study group, visit by study group interaction and the stratification factors. This model will be further adjusted for FS frequency at baseline. The relative and absolute treatment effect estimate and corresponding two-sided 95% CI, and p value of BCT compared with Befriending at Week 12 will be obtained to evaluate the primary hypothesis. In addition, an adjusted treatment effect will be obtained by including potential covariate (eg, depression) in the model.

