#### Secondary outcomes

Binary outcomes will be analysed similarly to the primary outcome; continuous outcomes will be analysed using a Longitudinal Data Analysis model.^37^ Any markedly skewed continuous outcomes will be transformed before analysis. The acceptability of BCT captured by a tailored self-report questionnaire provided after attending the Week 4 ‘booster’ session and adverse events will be reported by study group and visit.

The statistical models for the primary and secondary outcomes will provide valid inference in the presence of missing data if the missing data mechanism is missing at random.

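### The primary outcome is read from the absence of entries in an event-driven diary, so a returned diary that was not kept up cannot be told from true remission

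*Protocol article*

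**What the plan says.** Box 1 of the Protocol article gives the primary outcome as seizure remission at Week 12, "defined as seizure frequency of zero in the preceding 4 weeks", taken from the participant's seizure diary. Table 2 describes how that diary is kept: "Completed by the participant as seizures occur throughout the 24-week study period".

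The procedures around the diary are these:

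- **Prompts.** Table 3 lists "automated reminders sent weekly via text/email, or daily via MyCap". The wording of these reminders is not shown.
- **Return.** The diary paragraphs of the Measures section (printed after the PHQ-9 description) say that after the booster session, at the end of each monthly cycle up to Week 24, "participants will be contacted by study staff (emailed/texted) and asked to return their seizure diary".
- **Chasing.** If there is no reply to that message, "they will be telephoned by study staff within 5 days to assist gathering this data".
- **Derivation.** "A copy of the diary will be uploaded into REDCap and FS frequency for the preceding 4 weeks calculated". No rule is given for a blank or partly completed diary.
- **Review.** Box 2 has the physiotherapist review seizure frequency at the Week 4 booster. At Week 12 it lists adverse events and medication status for review by the research assistant, and no diary check.

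Under Statistical analysis, remission "will be analysed using a random intercept logistic regression model", and the models are said to be ones that "will provide valid inference in the presence of missing data if the missing data mechanism is missing at random".

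**The concern.** Success in this trial is the absence of something. In a diary filled in as events occur, an empty Week 9–12 window has two possible meanings: the participant had no seizures, or the participant had seizures and stopped writing them down. Nothing in the article separates the two once the page has been returned. Calculating a frequency from an empty event diary naturally gives zero, and zero is the definition of remission.

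Three things are at stake:

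- **Dilution.** False remissions in both arms shrink the difference and the relative risk.
- **Bias.** If recording effort differs by arm, the contrast is distorted. That is plausible but of unknown direction. Participants are not blinded. Only BCT participants keep a second diary, and the Adherence section has the physiotherapist contact them at Weeks 8 and 12 to return it, at either end of the primary window.
- **No rescue in the analysis.** A model valid under missing at random helps with outcomes recorded as missing. A non-recorder counted as zero is an observed success.

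This is a matter of data collection. A later analysis plan can decide how to classify a blank week, but it cannot recover whether that week was seizure-free.

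**Working it through.** **Inputs from the Sample size section:** remission 40% (BCT) and 20% (Befriending), 5% two-sided, 80% power, 25% drop-out, 110 per group.

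**Step 1: reproduce the plan's figure.** Two proportions, pooled variance under the null, no continuity correction:

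n = [1.960·√(2·0.30·0.70) + 0.842·√(0.40·0.60 + 0.20·0.80)]² / 0.20² = 81.2, so 82 per arm.

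82 / (1 − 0.25) = 109.3, so 110 per arm and 220 in total. This matches the plan. After 25% drop-out, 110 × 0.75 = 82.5 per arm remain, with power 80.6%. If all 110 per arm were analysed, power would be 90.5%.

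**Step 2: effect of blank diaries counted as zero.** Let m be the share of true non-remitters who return a diary with an empty window that is counted as zero. The documents give no value for m, so every value below is an assumption.

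Observed remission = p + (1 − p)·m

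For m = 10% in both arms:
- BCT: 0.40 + 0.60 × 0.10 = 0.46
- Befriending: 0.20 + 0.80 × 0.10 = 0.28
- Difference 18 points; relative risk 0.46 / 0.28 = 1.64

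Power = Φ[(difference − 1.960·SE₀) / SE₁], with SE₀ from the pooled proportion and SE₁ from the separate proportions. At 82.5 per arm, SE₀ = 0.0752 and SE₁ = 0.0739, so power = Φ[(0.18 − 0.1473) / 0.0739] = 67%.

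| m, BCT / Befriending | Observed remission | Difference (points) | Power, 82.5 per arm | Power, 110 per arm |
|---|---|---|---|---|
| 0 / 0 | 40% vs 20% | 20 | 81% | 90% |
| 5% / 5% | 43% vs 24% | 19 | 74% | 85% |
| 10% / 10% | 46% vs 28% | 18 | 67% | 79% |
| 15% / 15% | 49% vs 32% | 17 | 61% | 73% |
| 5% / 15% | 43% vs 32% | 11 | 31% | 39% |
| 15% / 5% | 49% vs 24% | 25 | 92% | 97% |

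**Step 3: no true effect.** With 20% true remission in both arms and m of 5% vs 15%, the observed rates are 0.20 + 0.80 × 0.05 = 24% and 0.20 + 0.80 × 0.15 = 32%. The chance of a two-sided rejection is then about 21% at 82.5 per arm and 26% at 110 per arm, against a nominal 5%.

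The two power columns bracket the case. The first assumes the full planned drop-out in addition to the blank diaries, and the second assumes no drop-out.

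**The case against.** The strongest reply has five parts.

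1. **No rule says a blank is remission.** A reader might infer from Table 2 and the derivation sentence that blank or abandoned diaries are scored as zero. The documents do not support that as fact: no sentence says how a blank is scored, and Table 2 does not say that entries are made only when a seizure occurs. This stands, and the point is limited to what could happen.

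2. **Abandoned diaries are chased.** A diary that is not returned leads to a telephone call, and nothing in the analysis section turns one that stays absent into a remission. This also stands. The exposure is the participant who stopped recording, had seizures and still returned the page.

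3. **The diary description may be incomplete.** The text mentions a second diary without a visible description of the first, and the wording of the reminders is not shown. The one MyCap prompt that is worded, for BCT homework, asks a yes/no question, so the seizure prompt may also need an answer. This is possible, and it is why the fix is conditional. Equally, no zero response is described for the seizure diary.

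4. **Scoring rules belong in the analysis plan.** That is true of the classification of blanks, but the plan cannot supply a confirmation that was never collected.

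5. **The magnitude is assumed.** It is. The unequal-rate scenarios use a threefold difference between arms that nothing in the documents establishes, and they show bias either way. The Week 12 Seizure Quality Questionnaire covers the same 4 weeks and could expose some false zeros, though the article does not assign it that use.

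**Conclusion.** The point holds in a limited form. As described, the primary outcome depends on empty space in an event-driven diary, with no described way to separate a true zero from non-recording once the diary is returned. Such a diary could be counted as remission. The article does not state that it will be, and unreturned diaries are outside the point.

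The size cannot be fixed from the documents. With 5% to 15% of non-remitters affected equally in both arms, power would be 74% to 61% at 82.5 per arm, or 85% to 73% at 110 per arm. At 10% it would be 67% or 79%. Unequal shares would bias the effect, and neither the direction nor the likelihood of that is known. A reader might infer that BCT's extra diary and contacts favour one arm, but the documents support only that recording effort may differ.

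It is worth acting on now. Recruitment began in February 2024 and is expected to run for 4 years, and the missing information cannot be recreated afterwards.

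**What to change.** First check the full diary instrument. If it already requires an explicit zero, stating so settles the collection point. Otherwise:

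- Turn the existing weekly text/email or daily MyCap reminder into a request for a seizure count, with 0 to be entered if there were none.
- Count Week 12 remission only when all four weeks are confirmed as zero, either by entry or by telephone. Extend the existing staff call to blank or incomplete diaries. The article assigns the call to study staff without saying whether they are blinded; it should be made by staff blinded to allocation.
- Any recorded seizure in the window means no remission. Weeks that are unconfirmed and contain no recorded seizure make the outcome missing, not zero.
- Use the Week 12 Seizure Quality Questionnaire as a consistency check on reported zeros.
- Run a sensitivity analysis for participants enrolled before the change, since they will have been measured by a different method.

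The cost is a form edit in REDCap and MyCap, a short derivation rule, some extra calls, a few more missing outcomes in place of possible false remissions, and a change of instrument during the trial.

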### Study hypothesis

We hypothesise that the proportion of patients with seizure remission, defined as FS frequency of zero in the preceding 4 weeks (recorded by the participant in a seizure frequency diary) at 12 weeks after initial treatment will be higher in the group of patients randomised to BCT compared with those randomised to control (Befriending).

Further, BCT will be as acceptable to patients and cost-effective compared with standard care for FS. In addition, we hypothesise that quality of life, work and social functioning, depression and anxiety symptoms, and hyperventilation tendency will improve more with BCT than control.

As an exploratory hypothesis, we expect hyperventilation preceding or during seizures will predict response to BCT, and that hyperventilation measured by expired carbon dioxide (CO_2_) will be clinically identifiable (by association with convulsive seizure phenomenology, childhood trauma history and increasing pre-ictal heart rate).

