## Methods and analysis

### Trial design

A 24-week, multicentre, individually-randomised, assessor-blinded, two-arm, parallel-group efficacy and acceptability trial of BCT versus control (Befriending) in 220 participants ≥16 years of age with FS. Eligible participants will be randomly allocated (1:1) to receive two sessions of either BCT or Befriending with a respiratory physiotherapist over a 4-week period. They will complete assessments at baseline (prior to commencing treatment) and 4 weeks, 12 weeks and 24 weeks post their initial session of BCT/Befriending. The trial will be conducted alongside their standard care (treatment as usual). Optional, longitudinal observational follow-up will be conducted 52 weeks, 78 weeks and 104 weeks after their initial treatment session.

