Box 2Trial schematicClinical assessment (neurologist)Functional seizures diagnosis confirmed by epileptologist.Participant informed of trial.Informed consent obtained OR obtain consent for study staff to follow-up and discuss.PrescreeningEligibility confirmed using prescreening questionnaire.Informed consent (if not completed by referring clinician).Baseline study questionnaires completed: Demographics, The Assessment of Quality of Life Eight Dimension (AQoL-8D), Generalised Anxiety Disorder Assessment (GAD-7), Patient Health Questionnaire, 9-item (PHQ-9), Multiscale Dissociation Inventory (MDI), Nijmegen, Toronto Alexithymia Scale, Resource Use Questionnaire (RUQ), Seizure triggers and control, Seizure quality, Work and Social Adjustment Scale (WSAS).Medical record data extracted.RandomisationPhysiotherapist contacts participant to inform them of their group allocation and schedule first session.Initial treatment session (Breathing Control Training/Befriending): baseline60 min, one-on-one session with physiotherapist, conducted at clinical care site (or Telehealth if required).Seizure frequency and adherence diary provided.Booster treatment session (Breathing Control Training/Befriending): week 430 min, one-on-one session with physiotherapist, conducted at clinical care site (or Telehealth if required).Adverse events, seizure frequency and adherence diary reviewed by physiotherapist.Research assistant (blinded) sends self-report questionnaires to participant via Research Electronic Data Capture (REDCap): *AQoL-8D, Acceptability, GAD-7, PHQ-9, MDI, Nijmegen, Seizure quality, WSAS.*Primary endpoint: week 12Research assistant (blinded) sends participant self-report questionnaires via REDCap: *AQoL-8D, Childhood Experience of Care and Abuse Questionnaire, GAD-7, PHQ-9, MDI, Nijmegen, RUQ, Seizure triggers and control, Seizure quality, WSAS.*Adverse events and medication status reviewed by research assistant.For eligible and willing participants, invited to complete Life Events and Difficulties Schedule.Follow-up: week 24Research assistant (blinded) sends participant self-report questionnaires via REDCap: *AQoL-8D, GAD-7, PHQ-9, MDI, Nijmegen, RUQ, Seizure quality, WSAS.*Participants randomised into the Befriending (control group) offered access to the BCT intervention.Observational follow-up: week 52, week 78 and week 104 (optional)Participants sent self-report questionnaires via REDCap: *AQoL-8D, GAD-7, PHQ-9, MDI, Nijmegen, RUQ, WSAS, seizure frequency (for previous 4*

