### Observational follow-up

52 weeks, 78 weeks and 104 weeks after their initial treatment session, participants will be sent online questionnaires (AQoL-8D, MDI, Nijmegen scale, FS frequency for the preceding 4 weeks, RUQ, WSAS) to complete. These longitudinal follow-up questionnaires will be optional, with the participant being able to opt out at any stage. These data will allow the researchers to observe FS health outcomes over an extended period of time and explore if there are any long-term benefits of BCT for FS.

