### Health service use databanks

For consenting Australian participants, data will be requested from Services Australia to ascertain use of MBS and PBS services. For consenting Victorian participants, data regarding hospital admissions, emergency department presentations and community health service use will be retrieved from CVDL. Both Services Australia and CVDL data will be requested for the period of study participation (ie, the 24-week randomised, controlled period), as well as 3 months prior to randomisation and will assist the health economic evaluation of the project and determining each participant’s TAU.

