### Statistical analysis

A formal detailed statistical analysis plan for the study will be written prior to unblinding of the database. All analyses will follow the intention-to-treat principle.

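### Week 12 and the seizure diary both start at the first treatment session, so a randomised participant who never attends has no defined primary outcome, despite the intention-to-treat statement

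*Protocol article*

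**What the plan says.** **Time origin.** Trial design dates the trial assessments "4 weeks, 12 weeks and 24 weeks post their initial session of BCT/Befriending". Box 1 (Outcomes) gives the primary outcome as "measured at Week 12 (12 weeks post the initial treatment session". The Study hypothesis uses the same origin: remission "at 12 weeks after initial treatment will be higher in the group of patients randomised to BCT". The optional long-term follow-up is also counted this way, at "52 weeks, 78 weeks and 104 weeks after their initial treatment session".

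**Order of events.** Baseline questionnaires come first, then randomisation. Under Randomisation in Box 2 (trial schematic, Measures), the physiotherapist "contacts participant to inform them of their group allocation and schedule first session". No maximum interval between these steps is stated.

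**Diary.** The participant's seizure diary is the stated source of the primary outcome. Box 2 lists it under the initial treatment session: "Seizure frequency and adherence diary provided".

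**Analysis.** The Statistical analysis section states: "All analyses will follow the intention-to-treat principle". The primary model is a random-intercept logistic regression with visit, group, their interaction and the stratification factors, further adjusted for baseline seizure frequency. The article says inference is valid if missing data are missing at random.

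**The concern.** The first session is a sensible origin for people who attend it. The difficulty is that it happens after randomisation and after the arm is known. Someone who hears the allocation and does not attend has no date from which Week 12 can be counted, and no passage says how that person would receive a diary.

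Baseline seizure frequency enters the model as a covariate, not as an outcome row. A participant with no post-baseline record therefore adds nothing to the likelihood. The missing-at-random statement helps only if non-start is unrelated to outcome once arm, site, Nijmegen stratum and baseline frequency are accounted for. Otherwise the model in effect treats non-starters as if they resembled the starters in their arm.

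The article gives reason to expect that non-start could differ by arm. The Introduction reports that many patients do not attend or complete psychotherapy. The Discussion suggests that BCT may be more acceptable than psychotherapy. The control is described as one designed for trials of talking therapies. At stake is whether the primary result compares the randomised groups or, in practice, those who started.

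**Working it through.** **1. The plan's own figure.** Inputs from Sample size calculation and recruitment target: 40% v 20% remission, 80% power, two-sided 5%, 25% drop-out. With pooled variance and no continuity correction:

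n = [1.96 × √(2 × 0.30 × 0.70) + 0.842 × √(0.20 × 0.80 + 0.40 × 0.60)]² / 0.20² = 81.2, so 82 per arm.

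82 / 0.75 = 109.3, so 110 per arm and 220 in total. The stated size reproduces, so this point is not about the sample size.

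**2. Effect of losing non-starters.** Let p be the remission rate among all randomised in an arm, f the share who never start, and r the remission rate among non-starters. The rate among starters is

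(p − f × r) / (1 − f).

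From the document: p = 40% (BCT) and 20% (Befriending), and 14% remission under treatment as usual as one value of r. Assumed, because the article gives no figure: f, and the other values of r. The value of r is taken to be the same in both arms.

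Worked case, f = 10% Befriending and 3% BCT, r = 14%:
- BCT: (0.40 − 0.03 × 0.14) / 0.97 = 40.8%
- Befriending: (0.20 − 0.10 × 0.14) / 0.90 = 20.7%
- Difference 20.1 points, a shift of +0.1.

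| Non-start, Befriending v BCT | r | BCT starters | Befriending starters | Difference | Shift from 20 |
|---|---|---|---|---|---|
| 10% v 3% | 5% | 41.1% | 21.7% | 19.4 | −0.6 |
| 10% v 3% | 14% | 40.8% | 20.7% | 20.1 | +0.1 |
| 10% v 3% | 35% | 40.2% | 18.3% | 21.8 | +1.8 |
| 15% v 5% | 5% | 41.8% | 22.6% | 19.2 | −0.8 |
| 15% v 5% | 14% | 41.4% | 21.1% | 20.3 | +0.3 |
| 15% v 5% | 35% | 40.3% | 17.4% | 22.9 | +2.9 |

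Differences are taken before rounding.

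**3. Dependence on which arm loses more.** The small shift at 14% partly reflects offsetting terms and holds only when Befriending loses more. With the pattern reversed and r = 14%:
- 10% BCT v 3% Befriending: 0.386 / 0.90 − 0.1958 / 0.97 = 42.9% − 20.2% = 22.7 points.
- 15% BCT v 5% Befriending: 0.379 / 0.85 − 0.193 / 0.95 = 44.6% − 20.3% = 24.3 points.

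**4. No true effect.** With 20% remission in both arms over all randomised, non-start of 15% BCT v 5% Befriending and no remission among non-starters, starters show 0.20 / 0.85 = 23.5% v 0.20 / 0.95 = 21.1%, a spurious +2.5 points. If non-starters remit at 30%, the figures are 18.2% v 19.5%, or −1.2. The sign therefore cannot be fixed in advance.

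**The case against.** **A starters-only analysis might be inferred, but the article does not define one.** It promises intention to treat, and non-attendance is not among the withdrawal grounds in Participant safety and withdrawal, so a non-attender remains in the trial. This stands: the conflict lies between the promise and what the data flow can deliver, not between two stated analysis sets.

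**Contact routes exist that do not obviously depend on attendance.** The blinded research assistant sends questionnaires through REDCap, diary reminders are automated, staff email, text and then telephone about unreturned diaries, and people who withdraw are asked their seizure frequency at an exit interview. Sessions can be held by telehealth, which makes non-start less likely. This also stands in part. These routes could reach a non-attender, so a total absence of data is a risk and not a certainty. But none supplies a time zero or says how the diary is issued without a session, and the exit interview can be declined and is not a Week 12 diary measure.

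**Fallback dates are detail for a fuller document.** In general that is fair, and an unseen analysis plan may handle missing outcomes. It cannot, however, recover diary data that were never collected, and the article does fix the origin and the diary hand-out.

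**The bias could be negligible.** At 14% remission among non-starters, with more non-start in Befriending, it is. A shift of nearly +5 points in that pattern needs 15% v 5% non-start and 50% remission among non-starters (39.5% − 14.7% = 24.8 points), which is above the 40% targeted for BCT and is not credible. The 25% drop-out allowance may cover the number lost, though not selective loss.

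**It might also be inferred that every data source runs from the first session.** It does not: the linked health-service data cover the randomised period "as well as 3 months prior to randomisation". That look-back does not conflict with the visit timing.

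**Conclusion.** The point holds for the primary outcome and the Week 4, 12 and 24 assessments. As written, a randomised non-attender has no defined Week 12, no stated route to a diary and no contribution to the primary model. That conflicts with the intention-to-treat statement and leaves room for loss related to arm.

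The size is unknown. If more people fail to start in Befriending (10% v 3% or 15% v 5%), the shift on a 20-point difference is about 0.1 to 0.3 points at 14% remission among non-starters, and about −1 to +3 points at 5% to 35%. Those ranges rest on assumed non-start rates, equal remission among non-starters in both arms, and 40% and 20% being rates over all randomised. They are not bounds, since the reverse pattern of non-start gives larger shifts. The case for acting is that the missing data cannot be recovered later and the remedy is cheap, not that a large bias has been shown.

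**What to change.** - Keep the first-session clock for people who attend.
- Issue the seizure diary and start its reminders at randomisation, for everyone.
- Set a fallback time zero for anyone who does not attend, such as the date of the first appointment offered.
- Collect Week 4, 12 and 24 data from that date and include these people in the primary analysis.
- Report non-starters by arm.

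**Cost.** A short protocol amendment, a date rule in REDCap and some extra chasing of non-attenders. Recruitment opened in February 2024, so the change would apply only from partway through, and earlier non-starters may remain without outcome data. The total of 220 does not change, provided that 40% and 20% are understood as rates over all randomised.

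Booking the first appointment before disclosing the arm, and giving the linked-data window the same origin, are optional and not needed for this fix.
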